## Abstract

**Background:**

Chemotherapy-induced peripheral neuropathy (CIPN) is one of the most common adverse effects of antineoplastic agents, ranging in prevalence from 19% to over 85%. Clinically, CIPN is a predominantly sensory neuropathy that may be accompanied by motor and autonomic changes of varying intensity and duration. The high prevalence of CIPN among cancer patients makes it a major problem for both patients and survivors, as well as for their health care providers, especially because there is currently no single effective method of preventing CIPN; moreover, the options for treating this syndrome are very limited.

Phycocyanin, a biliprotein pigment and an important constituent of the blue-green algae *Spirulina platensis*, has been reported to possess significant antioxidant and radical-scavenging properties, offering protection against oxidative stress, which is one of the hypothetic mechanisms, between others, of CIPN occurrence.

**Methods:**

Our hypothesis is that phycocyanin may give protection against oxaliplatin-induced neuropathy in the treatment of gastrointestinal cancers. Our trial will be a randomized double-blind placebo-controlled study with 110 randomized patients suffering from metastatic gastrointestinal adenocarcinoma including esogastric, colorectal, and pancreatic cancers. Patients are being followed up in the gastroenterology or oncology departments of seven French hospitals.

**Discussion:**

Due to the neuropathy, patients need to avoid injury by paying careful attention to home safety; patients’ physicians often prescribe over-the-counter pain medications. If validated, our hypothesis should help to limit neurotoxicity without the need to discontinue chemotherapy.

**Trial registration:**

ClinicalTrials.gov NCT05025826. First published on August 27, 2021.

**Supplementary Information:**

The online version contains supplementary material available at 10.1186/s13063-023-07071-z.

## Administrative information

Note: the numbers in curly brackets in this protocol refer to SPIRIT checklist item numbers. The order of the items has been modified to group similar items together (seehttp://www.equator-network.org/reporting-guidelines/spirit-2013-statement-defining-standard-protocol-items-for-clinical-trials/).

## Introduction

### Background and rationale {6a}

Gastrointestinal (GI) cancers account for 26% of the overall incidence of cancer and 35% of cancer-related deaths [1]. They mainly include esophageal and gastric carcinoma, colorectal carcinoma, pancreatic carcinoma, and hepatocarcinoma [2]. The drugs used most commonly as first-line therapy are platinum derivatives (cisplatin, oxaliplatin), 5-fluorouracil (5-FU), and other pyrimidine analogs (capecitabine), either administered as single agents or, frequently, in combination [2].

As with other chemotherapy drugs, the basic cytotoxic effect of platinum-based compounds (DNA damage) is not restricted to tumor cells, thus resulting in a variety of adverse effects.

Neurotoxicity in response to platinum-based therapy is the leading clinical entity that usually hampers platinum-based chemotherapy, aside from nephro- and hepatotoxicity. The most frequently reported manifestations of neurotoxicity are due to the clinical onset of peripheral neurotoxicity (numbness, tingling, or paresthesia in fingers and/or toes). With prolonged treatment, they gradually lead to disturbance of proprioception, which may result in ataxic gait [3]. The clinical manifestations of encephalopathy accompanying platinum-based therapy usually appear with an increase in cumulative dose [4]. Sensory manifestations of platinum compound-induced neuropathy are often accompanied by ototoxicity (mainly hearing loss). Note that carboplatin neurotoxicity is negligible compared to cisplatin and oxaliplatin.

The root cause of many adverse effects and the organ injury of platinum-based drugs is the generation of reactive oxygen species (ROS) [5]. The increase in ROS production associated with neuronal mitochondrial dysfunction was described as a potential mechanism of platinum drug neurotoxicity. Therefore, antioxidant supplementation to reduce ROS, or to alleviate the effects of ROS, could also have a significant influence on the neurotoxic adverse effects of platinum drugs.

In conclusion, administration of oxaliplatin at therapeutic dose could induce neuropathy. Accordingly, an important therapeutic strategy is to reduce the oxaliplatin dose. However, once the therapeutic dose of oxaliplatin is reduced, the therapeutic effects can fall significantly.

Phycocyanin (PC) is one of the main pigments of the algae *Spirulina*, which also contains proteins, β-carotene, assimilable iron, γ-linoleic acid, and vitamin B12, and is used as a dietary supplement. The chemical structure of PC is very close to the structure of bilirubin, a degradation product of hemoglobin. Bilirubin is known to be an important physiological antioxidant that combats reactive oxygen species.

In 1998, Cuban researchers described the antioxidant activity of PC [6] for the first time. These authors determined that PC was able to scavenge the hydroxyl radical (OH^-^), the alkoxyl radical (RO), and the superoxide anion (O_2_^−^). It was also able to inhibit lipid peroxidation [6]. In addition, they described the anti-inflammatory properties of PC for the first time [7].

In 2018, Renugadevi et al. revealed that the PC pigment could be a promising antioxidant compound and with further study, that it has the potential as an antioxidant agent to overcome oxidant-induced diseases [8].

Our hypothesis is to test Spirulina liquid extract that has been greatly enriched with PC (SLPC) in patients with gastrointestinal cancer and treated with platinum salts, to reduce or cancel out the neuropathy associated with this treatment, which is still an unresolved medical need. The SLPC contained in the food supplement SPIRULYSAT® (produced by AlgoSource) has already been tested for metabolic syndrome (NCT02817620). Studies of SPIRULYSAT® in the murine model of non-alcoholic steatohepatitis have shown very strong anti-oxidant activity [9]. The SLPC used in this protocol will be five times more concentrated but is still produced by the same laboratory (PHYCOCARE®).

In brief, firstly, it is generally accepted that no pharmacologic agent has been definitively shown to prevent platinum salt-induced neurotoxicity [10]. Secondly, although duloxetine, a non-selective serotonin reuptake inhibitor antidepressant with non-opioid pain-relieving properties, has been shown to be effective in ameliorating neuropathic pain, clinical experience has not, to date, validated the trial data [11]. Thirdly, as already mentioned, the dose of platinum salts can be reduced so as not to induce neuropathy, possibly leading to a drastic reduction in the therapeutic effects. Fourthly, spirulina and more precisely PC has anti-oxidant effects and in murine models, it protects the kidneys from the nephrotoxic effects of cisplatin [12].

Taken together, we hypothesize that PC, and more precisely SLPC (contained in PHYCOCARE® - AlgoSource) may have protective effects against oxaliplatin-induced neuropathy in the treatment of GI cancer including esogastric, colorectal, and pancreatic cancers. Our trial will be a double-blind randomized placebo-controlled study.

### Objectives {7}

The primary objective is to demonstrate a 50% decrease in neurotoxicity grades of 2 or above at cycle 9 (4 months after the start of oxaliplatin-based chemotherapy) in the SLPC arm.

The secondary objectives are to compare the following in both arms:➢ Percentage of patients who stopped oxaliplatin due to neurological toxicity➢ Percentage of patients with an oxaliplatin dose decrease➢ Neurological toxicities according to the Common Terminology Criteria for Adverse Events (CTCAE) v5.0➢ Overall toxicity (including hematological toxicity, gastrointestinal toxicity, etc.)➢ Patient’s quality of life according to the EORTC-QLQ-C30 questionnaire

### Trial design {8}

PROPERTY is a non-comparative, randomized (ratio 1:1), double-blind, multicenter placebo-controlled study. The trial was constructed like a phase 2 drug trial and is not powered for direct comparison between the two arms.

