### Sample size {14}

Simon’s two-stage design [15] will be used. The null hypothesis that the true response rate is 0.60, the proportion of neurotoxicity targeted, will be tested against a one-sided alternative. In the first stage, 31 patients will be accrued. If there are 18 patients or fewer with grade 1 neurotoxicity among these 31 patients in the SLPC arm, the study will be halted. Otherwise, 24 additional patients will be accrued, making a total of 55. The null hypothesis will be rejected if 38 or more responses are observed in 55 of the SLPC arm patients. With a type I error rate of 0.05 and a power of 0.90, 55 patients will be enrolled in each arm, that is to say, 110 patients.

All the previous hypotheses account for a lost-to-follow-up rate at 4 months of 20%.

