## Discussion

Although oxaliplatin has an improved overall survival rate [18, 19], oxaliplatin-induced peripheral neuropathy (OIPN) remains a treatment-limiting factor [20]. Some degree of OIPN occurs in nearly all patients [18] and approximately two thirds will have symptoms 1 year post treatment or beyond [21]. OIPN has been reported as dose dependent, with symptoms more likely to occur as the cumulative dose exceeds 780–850mg/m^2^. Unlike acute OIPN, which is transient, chronic OIPN can persist for months or years [22] and includes pain, numbness, and dysesthesias as well as gait disturbances that lead to reduced quality of life and function [23].

The US National Cancer Institute’s Symptom Management and Health-Related Quality of Life Steering Committee has announced that CIPN is a priority area of translational research in cancer care [24]. Even the latest literature data clearly indicate that although numerous preventative therapies were tested for their potential utility for CIPN alleviation, this clinical entity currently is still not preventable, and many strategies tested were found to be ineffective [25, 26].

At present, based on meta-analyses of clinical trials, no drug can be proposed as a gold standard to either prevent CIPN or treat its symptoms, and chemotherapeutic drug dose modification remains the only preventative strategy [27].

Our trial will provide a significant clinical gain for the patient if our hypothesis is correct. The oncologist will be able to continue the same treatment at the same dose with a therapeutic response to neuropathy.

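### The primary objective is to demonstrate a 50% decrease in grade ≥2 neurotoxicity, but the decision rule only tests the SLPC arm against a fixed 0.60

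*Protocol article*

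**What the plan says.** - **Objectives {7}:** "The primary objective is to demonstrate a 50% decrease in neurotoxicity grades of 2 or above at cycle 9", in the SLPC arm. The reference for the decrease is not named. The secondary objectives are expressly comparisons of the two arms.
- **Trial design {8}:** "PROPERTY is a non-comparative, randomized (ratio 1:1), double-blind, multicenter placebo-controlled study". It adds that the trial "is not powered for direct comparison between the two arms".
- **Sample size {14}:** "The null hypothesis that the true response rate is 0.60, the proportion of neurotoxicity targeted, will be tested against a one-sided alternative". No alternative rate is given. At stage 1, "If there are 18 patients or fewer with grade 1 neurotoxicity among these 31 patients in the SLPC arm, the study will be halted". At the end, "The null hypothesis will be rejected if 38 or more responses are observed in 55 of the SLPC arm patients". The stated type I error is 0.05, the power 0.90, and the size 55 per arm.
- **Interim analyses {21b}:** futility is also judged on SLPC responders alone.
- **Outcomes {12}** and **Statistical methods {20a}:** the primary endpoint is defined in both arms. Prevalence of grade ≥2 is estimated in both arms by a mixed regression with a random centre effect, then adjusted for risk factors. No difference, ratio or test between arms is named for it, although several secondary outcomes are compared between arms.

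**The concern.** A decrease needs a reference. If the reference is placebo, no planned primary contrast addresses it. If it is the fixed rate, rejecting the null shows only that the SLPC response rate exceeds 0.60, which is much weaker than a halving of toxicity.

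What is at stake is how a positive result is read. Under the plan as written, a trial that meets its rule could be reported as having met an objective that the rule does not test. Success would also depend on 0.60 being right for these patients at this visit. The randomised placebo arm could check that, but it does not enter the decision.

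**Working it through.** **Inputs.** From Sample size {14}: null rate 0.60; stop if 18 or fewer of 31; reject if 38 or more of 55; 20% loss at 4 months. From Objectives {7}: a 50% decrease.

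Assumptions:
- Responders are patients with grade 0-1.
- Reading A: 0.60 is the rate free of grade ≥2, so null toxicity is 40% and the halved rate 20%.
- Reading B: 0.60 is the toxicity rate, halved to 30%.
- 44 evaluable per arm = 55 × 0.80.

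**1. The plan's own figures.** P(pass | p) = Σ over x = 19 to 31 of P(X₁ = x) × P(X₂ ≥ 38 − x), with X₁ ~ Bin(31, p) and X₂ ~ Bin(24, p).
- At p = 0.60 this gives 0.104, not 0.05.
- At p = 0.80 (assumed) it gives 0.980, not 0.90.

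The stated error rates are therefore not reproduced. That is a separate fault in the boundary, but it affects step 3.

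**2. What success means under reading A.**
- Toxicity at the boundary: (55 − 38)/55 = 17/55 = 30.9%, exact 95% CI 19.1% to 44.8%.
- Relative fall from 40%: 1 − 0.309/0.40 = 22.7%.
- An observed halving would need 11/55 = 20%.
- A true 25% fall (toxicity 30%, response 0.70) passes with probability 0.615.

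**Reading B.** 17/55 would be a fall of 1 − 0.309/0.60 = 48%, close to the objective. But the null response rate would then be 0.40. The chance of 17 or fewer toxicities in 55 at a toxicity rate of 0.60 is about 0.00001, and the probability of passing at 30% toxicity is 0.615. Neither fits the stated 0.05 and 0.90, so the rule fits reading A better, though the text leaves it open.

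**3. Dependence on the fixed rate.** Suppose SLPC is inert and the true untreated grade 0-1 rate differs from 0.60. The rates below are illustrative; the document gives none.

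| True untreated grade 0-1 rate | Pass, ≥38/55 (as stated) | Pass, ≥40/55 |
|---|---|---|
| 0.60 | 0.104 | 0.034 |
| 0.65 | 0.31 | 0.14 |
| 0.70 | 0.62 | 0.39 |
| 0.75 | 0.87 | 0.71 |

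The last column keeps the same stage 1 and uses a final boundary that holds 5%. It shows how much of the risk remains once the boundary fault is removed.

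**4. What a between-arm estimate could deliver.** Half-width = 1.96 × √{[p₁(1−p₁) + p₂(1−p₂)]/n}. For 40% vs 20% at n = 55: 1.96 × √(0.40/55) = 0.167. Power = Φ{[d − z√(2p̄(1−p̄)/n)] / √([p₁(1−p₁) + p₂(1−p₂)]/n)}, with d the difference, p̄ the mean rate, and z = 1.96 (two-sided 5%) or 1.645 (one-sided 5%).

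| Rates | n per arm | Half-width | Power, two-sided | Power, one-sided |
|---|---|---|---|---|
| 40% vs 20% | 55 | 17 points | 63% | 75% |
| 40% vs 20% | 44 | 19 points | 54% | 66% |
| 60% vs 30% | 55 | 18 points | 90% | 94% |
| 60% vs 30% | 44 | 20 points | 82% | 89% |

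**The case against.** **The design is declared.** A randomised, non-comparative phase 2 trial with a Simon rule in the active arm is a recognised choice. The primary objective is worded for the SLPC arm, and comparison is reserved for the secondary objectives. This stands: the design is not the fault. What remains is that the verb demonstrate and the figure of 50% do not match the rule.

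**The placebo arm is used.** A reader might infer that it has no part in the primary question. The document does not support that: grade ≥2 prevalence is estimated in both arms to meet the main objective, so a wrong reference rate could become visible. The narrower point holds. Placebo data enter neither the futility rule nor the success rule, and no contrast is named. An analysis plan not shown here may add one, but it would not remove the mismatch between the stated objective and the stated rule. Nor is the missing source for 0.60 counted as a fault, since an article may leave that to the full protocol.

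**Any test can succeed with an observed effect below its design effect.** True, so 23% at the boundary does not invalidate the rule as a go/no-go. It does show that passing the rule is not a demonstration of 50%.

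**The dose argument is not supported.** Cycle 9 day 1 follows at most 8 × 85 = 680 mg/m². The Discussion describes neuropathy "with symptoms more likely to occur as the cumulative dose exceeds" 780-850 mg/m². A reader might infer that untreated toxicity at that visit is below 40%. But that sentence concerns symptoms rather than grade ≥2 rates, no rate at 680 mg/m² is given, and the section on choice of comparators {6b} places the onset of chronic toxicity at cycles 8-10. The point here does not rely on it.

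**Conclusion.** The objective and the decision rule do not match and should be reconciled. Meeting the rule would show that the SLPC arm does better than a fixed 0.60. It would show neither a halving against placebo nor, under reading A, a halving against the fixed rate, because success starts at a 23% relative fall.

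The size of the problem rests on assumptions. The meaning of 0.60 is ambiguous and the alternative rate is unstated, so 40% vs 20% is a reading and not a fact of the plan. The untreated rates of 0.65 to 0.75 are illustrative. Part of the 0.31 to 0.87 pass probability for an inert product comes from the separate boundary fault; 0.14 to 0.71 remains when the boundary holds 5%. This should be corrected, but it is no reason to abandon the design.

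**What to change.** 1. State whether 0.60 is a response rate or a toxicity rate. Reword the primary objective to what the Simon rule tests, namely that the SLPC arm does better than that fixed rate, and keep the rule as the go/no-go decision.
2. Pre-specify the SLPC-placebo risk difference and risk ratio for grade ≥2 at cycle 9 day 1, with 95% CI, as the estimate on which any claim of a decrease must rest. Adjust for baseline neuropathy grade and age group, with centre as a random effect. Do not stratify over every randomisation cell: 7 centres × 2 × 2 = 28 cells for 110 patients is about 4 per cell.
3. State the precision of that estimate conditionally, using the table in the working, once the meaning of 0.60 is settled.

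The cost is revised wording and one additional pre-specified estimate from data already collected, with no extra patients or visits. The downside is saying openly that the comparison is imprecise, and under 40% vs 20% clearly underpowered.

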## Methods: participants, interventions, and outcomes

### Study setting {9}

This study is a French multicenter trial. Patients will be recruited from seven teaching hospital gastroenterology departments: CHU Nantes, Foch Hospital, Vendée Departmental Hospital, Estaing Hospital, Saint-Grégoire Private Hospital, Saint Nazaire Hospital, Georges and François Leclerc Center.

### Eligibility criteria {10}

The study population only includes patients with histologically or cytologically proven gastrointestinal cancer, including esogastric, colorectal, and pancreatic cancers, where the plan is to treat them with oxaliplatin. Other inclusion criteria are patients aged 18 years and over, a negative pregnancy test for women of child-bearing potential, patients with an ECOG performance status of 0 or 1 [13], and life expectancy ≥12 weeks. The results of laboratory analyses and the other inclusion criteria are shown in Table 1, as are the exclusion criteria. The main exclusion criteria are patients with known meningeal or brain metastases previously treated for their metastatic cancer or treated with oxaliplatin, and suffering from peripheral neuropathy.

**Table 1 Tab1:** Inclusion and exclusion criteria

Inclusion criteria	Exclusion criteria
• Male or female with the age > or = to 18 years old. • Negative pregnancy test for women with child-bearing potential if applicable (without hysterectomy for example) • Information given to the patient who must have signed informed consent • Patient with Histologically or cytologically proven gastrointestinal adenocarcinoma including oesogastric, colorectal, and pancreatic cancers and planned to be treated with oxaliplatin • Patient with metastasic disease not previously treated • Previous radiotherapy is authorized if discontinued ≥15 days prior to randomization • Sites of disease evaluated within 42 days prior C1 day 1 of chemotherapy with thoracic-abdominal-pelvic CT scan (or abdominal-pelvic MRI and chest X-ray) • Patient with ECOG Performance status 0 or 1 • Patients with a Life expectancy ≥12 weeks • Laboratory results: ° Hematologic function: ▪ Polynuclear neutrophils ≥ 1.5.10^9^/L ▪ Platelets ≥100.10^9^/L ▪ Haemoglobin ≥9 g/dL ° Hepatic function: ▪ Transaminases ≤2.5 times upper limit of normal (ULN) (≤5 ULN in case of hepatic metastases), ▪ Alkaline phosphatases ≤2.5 × ULN (≤5 ULN in case of hepatic metastases), ▪ Total bilirubin ≤1.5 × ULN ° Renal function: ▪ Creatinemia clearance >50 ml/min (Cockcroft and Gault) • Patient with Public Health insurance coverage	• Patients with phenylketonuria • Patients with known meningeal or brain metastases • Patient previously treated for their metastatic cancer • Patient previously treated with oxaliplatin • Patient with specific contraindication or known hypersensitivity to spirulina • Patient with specific contraindication or known hypersensitivity to oxaliplatin. • Known allergy or hypersensitivity to antibodies or any preservatives if patient is treated with a monoclonal antibody combined to chemotherapy (bevacizumab or cetuximab or panitumumab or nivolumab), • Patient with clinically significant coronaries affection or myocardial infarction within 6 months prior to randomization. • Patient with peripheral neuropathy >1 (CTCAE scale version 5.0). • Patients with known dihydropyrimidine dehydrogenase (DPD) deficiency. • Patient with acute intestinal obstruction or sub-obstruction, history of inflammatory intestinal disease or extended resection of the small intestine or presence of a colic prosthesis. • Patient with unhealed wound, active oesogastric or duodenal ulcer, or bone fracture • Patient with an history of abdominal fistulas, trachea-esophageal fistulas or any other grade 4, gastro-intestinal perforations or non-gastrointestinal fistulas or intra-abdominal abscesses during the 6 months before randomization. • For patient treated with bevacizumab: patient with uncontrolled arterial hypertension (systolic pressure >150 mmHg and/or diastolic pressure >100 mmHg) with and without antihypertensive medication. Patients with high hypertension are eligible if antihypertensive medication lowers their arterial pressure to the level specified by the inclusion criterion. • Patient with an history of hypertensive crisis or hypertensive encephalopathy • Patient with other concomitant malignancy or history of cancer (except in situ carcinoma of the cervix, or non-melanoma skin cancer, treated with curative intent treatment) except if considered in complete remission for at least 2 years before randomization • Existence of any other pathology, metabolic problem, anomaly during the clinical examination or biological anomaly which may reasonable suspect an underlying pathology which would contra-indicate the use of the study medication or any other risk of complication related to the treatment. • Any treatment including an experimental drug, or participation in another clinical trial within 28 days before randomization. • Pregnant women, or women who could possibly be pregnant (or who expect to fall pregnant within 6 months of the end of treatment), or who are breast feeding are not eligible. • Men and women of child-bearing potential who do not accept to use a highly effective contraceptive (as per currently acceptable institutional standards) or abstinence during the study and for the 6 months after the last administration of the study treatments. • Persons deprived of liberty or under guardianship. • Psychological, familial, sociological or geographical condition potentially hampering compliance with the study protocol and follow-up schedule
